## Abstract

**Background:**

With the burden of mental illness estimated to be costing the English economy alone around £22.5 billion a year [1], coupled with growing evidence that many mental disorders have their origins in adolescence, there is increasing pressure for schools to address the emotional well-being of their students, alongside the stigma and discrimination of mental illness. A number of prior educational interventions have been developed and evaluated for this purpose, but inconsistency of findings, reporting standards, and methodologies have led the majority of reviewers to conclude that the evidence for the efficacy of these programmes remains inconclusive.

**Methods/Design:**

A cluster randomised controlled trial design has been employed to enable a feasibility study of 'SchoolSpace', an intervention in 7 UK secondary schools addressing stigma of mental illness, mental health literacy, and promotion of mental health. A central aspect of the intervention involves students in the experimental condition interacting with a young person with lived experience of mental illness, a stigma reducing technique designed to facilitate students' engagement in the project. The primary outcome is the level of stigma related to mental illness. Secondary outcomes include mental health literacy, resilience to mental illness, and emotional well-being. Outcomes will be measured pre and post intervention, as well as at 6 month follow-up.

**Discussion:**

The proposed intervention presents the potential for increased engagement due to its combination of education and contact with a young person with lived experience of mental illness. Contact as a technique to reduce discrimination has been evaluated previously in research with adults, but has been employed in only a minority of research trials investigating the impact on youth. Prior to this study, the effect of contact on mental health literacy, resilience, and emotional well-being has not been evaluated to the authors' knowledge. If efficacious the intervention could provide a reliable and cost-effective method to reduce stigma in young people, whilst increasing mental health literacy, and emotional well-being.

**Trial registration:**

ISRCTN: ISRCTN07406026

## Background

There is growing pressure on schools in England to address stigma and misconceptions of mental illness [2-5] as well as increasing emotional well-being [6,7] in addition to traditional academic curricula. Currently there is little agreement as to what approach might most successfully address these issues [9-11].

Over half of all lifetime mental disorders have their onset during childhood and adolescence [12] yet young people's knowledge of mental illness is often incomplete [13] or influenced by sensationalised reports in the media [14]. Developmentally, adolescence is a complex period, with the majority of young people experiencing some level of distress or emotional problems. The adolescent brain has been shown to confer higher risk for mental illness due to a difference in the maturation of the developing brain and the adolescent emotional and cognitive systems [15]. Adolescents also experience high levels of schizotypal thinking [16], something which among adults is related to high vulnerability to mental illness [17].

Individuals with mental illness experience discriminatory attitudes in almost all areas of their lives [18,19], and stigma, alongside poor mental health literacy, can increase barriers to help-seeking [20,21]. Prevalence rates for psychotic disorders such as schizophrenia increase rapidly between the ages of 15 to 17 [12] with children and adolescents who experience early onset anxiety disorders such as phobias and separation anxiety disorder more likely to develop co-morbid disorders of substance use, later-onset anxiety, or mood [12]. Earlier age of onset for many mental illnesses is also correlated with greater severity [22], persistence [23] and increased resistance to treatment [24].

Young people themselves report that they would like to receive more information regarding mental health. Both Kidger et al. [25] and Woolfson et al. [26] found that students stated that they were dissatisfied with the mental health education they were receiving. Olsson and Kennedy [13] found that less than 30% of students recalled any discussion of mental health during school lessons, despite the fact that mental health education was mandatory in the area their research was conducted.

There is growing evidence to suggest that early interventions designed to optimise well-being or reduce mental illness and initiated during childhood and adolescence may help reduce mental health problems in later life [27-29]. The UK National Healthy Schools Programme attempts to address this, and advocates increasing emotional health and well-being (EHWB) support for students [30]. Schools engaged in this programme are expected to address subjects related to social skills and emotional health to their curriculum with targets including 'combating stigma and discrimination'; and 'encouraging the participation of children and young people in activities designed to build their confidence and self esteem' to achieve National Healthy Schools Status. There is however, no obligation for schools to take part and some remain uninvolved. Additionally, with lack of monitoring and threat of further funding cuts, the current programme appears vulnerable.

### Previous interventions

Reducing stigma and discrimination of mental illness, improving mental health literacy, reducing a particular mental illness, or promoting resilience are all popular methods for tackling mental health issues in schools [31-40]. Such interventions often demonstrate significant benefits such as reducing stigma, conduct problems and increasing prosocial behaviour [41], challenging negative opinions of psychosis [42], and can have a positive impact on interrelated factors such as school achievement, school climate, and reduced emotional behavioural and disciplinary problems [43-45]. The abundance of interventions are however, not easily comparable, and identifying which components of an intervention are successful, and which components lack utility, is often not possible. This has led to some large-scale interventions being instigated without a clear understanding of the likely efficacy of trial components. For example the *BeyondBlue *[46] trial in Australia included 50 schools in a five year intervention aimed at reducing and preventing depression and reported flat results [47]. Feasibility trialling and careful evaluation is needed to capture the potential problems as well as benefits of school interventions prior to the widespread dissemination of larger scale projects [9,48,49].

Many systematic reviews now concur that whole school approaches are the most effective model and emphasise the need to promote mental health universally rather than solely targeting the reduction of mental illness [11,50,51]. A greater investment in long-term approaches are also favoured by reviewers [11,52] and it has been suggested that future research should include more detailed analysis of demographic variables such as ethnicity and gender [9].

Regarding stigma and mental health literacy, fewer systematic reviews have been conducted into school-based studies. Kelly et al.'s [21] review concluded that for adolescents, good mental health literacy is associated with more positive outcomes for emotional well-being but add a caveat that very few school interventions to improve mental health literacy have been evaluated and even fewer *well *evaluated. Pinfold et al.'s [53] systematic review suggested that contact with individuals who describe personal experience of mental illness was more likely to lead to reductions in reported stigma; in contrast, a systematic review by Schachter et al. [48] failed to find any 'even remotely ideal investigation[s] whose results regarding possible benefits we can confidently accept as being reliable and valid' (p. 22). Schachter et al. criticised studies for a range of reasons including; inadequate study descriptions; poor research methodology; inadequate interventions; and failing to measure or control for relevant baseline characteristics of participants. Funding is also an issue in the present climate, with programmes designed to impact upon mental health issues in schools needing to demonstrate value for money as well as reliable and consistent effect sizes [9,54]. In summary, further well-designed research in these fields is warranted.

### Contact and stigma

Corrigan et al. [55] identify three strategies for challenging stigmatising attitudes and prejudice towards mental illness: 'protest', 'education', and 'contact'. 'Protest' involves condemning prejudicial attitudes; if a company were employing an advertising campaign that was deemed to be stigmatising, public protest may encourage changing of the advert, thus suppressing the stigmatising attitude. 'Education' seeks to encourage an increase in knowledge and awareness regarding mental illness, thereby dispelling myths in the belief that the more individuals understand the less prejudiced they will be. 'Contact' reasons that the more contact an individual has with someone who has experienced mental illness, the less stigmatising they will be, although the relationship is correlational - it may equally be the case that those who hold less stigmatising attitudes towards mental illness are happier to have contact with individuals experiencing mental illness [55]. Rusch et al. [56]note that if contact is employed to facilitate attitude change then this must be carried out under a controlled set of circumstances if the best possible outcome is to be achieved, otherwise the intervention may have a negative rather than positive outcome. Allport [57] who first proposed the contact hypothesis, similarly claimed that contact needed to involve individuals of equal status with the 'in' and 'out' groups working together rather than in competition with one another. Of protest, education, and contact, Corrigan et al. argue that contact is the most effective, followed by education, with protest having little significant impact on participants. Like Minds [19] add that contact married to education is a powerful combination for combating stigma.

Contact has been employed as a strategy to reduce stigma and increase understanding of mental health issues in a number of studies with adults [55,58] but rarely in school interventions [53,56]. Results have however shown promise, and contact may be a way of increasing the impact of interventions by facilitating engagement and overcoming barriers to learning. To date, contact has not been utilised to improve mental health literacy and emotional well-being in young people, but there is some evidence to suggest that it might have a favourable effect as two recent qualitative studies have indicated that young people wish to be taught about emotional well-being and mental health issues by someone who has lived experience of mental illness [25,26].

### The current study

The SchoolSpace intervention programme has been designed to measure the impact of an educational intervention on three core targets: reduction in stigma related to mental illness; mental health literacy; and promotion of mental health, with reduction in stigma related to mental illness being the primary outcome. Previous research has suggested that these may be interlinked [41]. For example, someone who doesn't *understand*, or is *prejudiced *against mental illness, may not seek help [20,21], leading them to be less *resilient*. The primary research question asks; 'is education in combination with contact better than education alone for reducing stigma?' Based on previous research [26,53] it is hypothesised that participants in the contact and education condition will report significantly reduced stigma towards mental illness compared with participants in the education only (control) condition.

Secondary research questions relate to how contact in combination with education may influence participants' a) mental health literacy, and b) emotional well-being and resilience, compared to education alone. In addition to this the trial will assess any influence of contact on attitudes to help-seeking. Previous research has found that stigma is a major barrier to help-seeking [20], and that low mental health literacy can lead to a delay in help-seeking [34]. It is therefore hypothesised that a reduction in stigma and increased mental health literacy will be associated with an increase in positive attitudes towards help-seeking.

Additionally, schizotypal thinking, which is linked to vulnerability to mental illness [17] and is common during adolescence [16] will also be measured. This addresses whether higher rates of schizotypal thinking in adolescence are linked to adolescents' increased vulnerability to developing mental illness compared to other age groups, or if such thinking patterns are developmental in some way [59]. If they are a sign of an adolescents increased vulnerability to mental illness then with increased resilience and increased mental health and emotional well-being, we hypothesise that rates of schizotypal thinking should reduce in participants. However, if schizotypal thinking is developmental than we might expect to see the opposite trend, with schizotypal thinking unaffected by any changes in mental well-being or resilience.

## Method/Design

SchoolSpace is a randomised controlled trial with two conditions: an experimental condition which includes contact with a young person with lived experience of mental illness as well as education, and an active control condition, which includes education but no contact. Measures will be taken 3 weeks prior to the intervention, and at both 2 weeks and 6 months post intervention. Random allocation will take place at the level of school and blocking will be used to randomly stratify classes to different conditions. Random allocation will be independent and concealed. Randomisation will be undertaken by an individual independent of the research team, and will take place after pre-test. The intervention has been designed in accordance with CONSORT guidelines [60,61].

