### Development and piloting of the intervention

Original intervention materials were developed by [name], [name] and [name] in collaboration with teachers and service-users with additional educational resources evolved from the work of [name] O'Reilly [62] and the Staffordshire Changes YP mental health programme [63]. Focus groups were also conducted with young people by [name] to aid the development of the programme. Interventions tend to be more successful if they are delivered over time, rather than in one intensive session [9], however the current intervention is a feasibility trial, and due to the constraints of resources, it was decided that a one-day intervention would be used, with the expectation that the intervention will be developed into a longer term intervention plan for evaluation in the future, should it prove to be successful.

The intervention was piloted in one school to assess the practicality; timings, level of pitch, and suitability of materials for the target age group. Classes were randomised to the Education and Contact condition and Education Only conditions. Procedure of the pilot intervention is identical to the feasibility trial.

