### Procedure

#### Stage 1; consent and pre-test

Schools in the Birmingham area will be approached and invited to take part in the research, drawn from the full range of socio-economic and socio-cultural settings. Once a school has agreed to participate, consent letters will be sent out to the parents of all participating students.

Pre-intervention questionnaires will be completed 3-4 weeks prior to the intervention day. A self-generated code will be used to match participant answers over time whilst preserving anonymity. This code has a reported 92% success rate [64]. It must therefore be expected that a minimum of 8% of participants may be lost over time due to mistakes in the generation of this code. Teachers will have over a week to collect questionnaire data in order to minimise loss of data through student absences from school.

Class randomisation to condition will take place after pre-test, at the level of school.

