#### Stage 2; the intervention

Participants are taught within their usual classes. Each class is facilitated by 2-4 staff including a lead who will be a NHS mental health specialist, and a teaching assistant. Facilitators in the education and contact condition include at least one facilitator who has lived experience of mental illness. As well as the facilitators a minimum of one teacher from the school will be present in each class. Fidelity of the intervention delivery between conditions will be assessed with a pre-developed checklist on the intervention day. One class per condition, per school will be assessed for fidelity by [name]

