### Analysis

Data will be analysed applying appropriate general linear models. In order that the clustering of the sample does not bias the analysis pre-test outcome measures will be entered as a covariate. Subgroup analyses will look at gender, ethnicity, religion, and mental health status of self, family, and friends in relation to the hypotheses and data analysed using appropriate general linear models. Intention to treat analyses will be used.

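### Classes are randomised within schools, but the stated analysis leaves clustering to the pre-test covariate and names neither class nor school

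*Protocol article*

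**What the plan says.** **Allocation.** The abstract calls the study a cluster randomised trial. Method/Design says: "Random allocation will take place at the level of school and blocking will be used to randomly stratify classes to different conditions". Stage 1 of the Procedure says: "Class randomisation to condition will take place after pre-test, at the level of school". On the pilot, the development section reports: "Classes were randomised to the Education and Contact condition and Education Only conditions", and adds: "Procedure of the pilot intervention is identical to the feasibility trial". Stage 2 plans the fidelity check so that "One class per condition, per school will be assessed for fidelity", which requires both conditions in every school. The sample size section takes a class of about 30 pupils as the cluster, with an ICC of 0.037.

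**Analysis.** The Analysis section calls for general linear models whose form is left open. It then says how clustering is to be kept from biasing the result: "pre-test outcome measures will be entered as a covariate". It mentions no class effect, school effect, cluster-robust variance or class-level summary.

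**The concern.** The groups that were randomised, and the blocks within which they were randomised, should appear in the model that compares the arms. Here the class is the randomised group and the school is the block, and the Analysis section names neither. It does address clustering explicitly, but with a tool that does not do the job.

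Adjusting for a pupil's own pre-test score removes the part of the class differences that the score predicts. It does not make classmates independent given that score. New class-level variation can also arise after pre-test, because each class has its own group of 2-4 facilitators and its own teacher in the room (Stage 2). If pupils are analysed as independent, the standard error of the contact effect is too small.

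The section on the current study sets up a significance claim: stigma is expected to be significantly lower with contact plus education than with education alone. An inflated type I error therefore bears directly on the primary conclusion.

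**Working it through.** **1. Which unit does the sample size use?** Inputs from the plan: ICC 0.037, about 30 pupils per class, effect sizes 0.3 and 0.2. Two-sided 5% and 80% power are assumed, since neither is stated.

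- Per arm without clustering, n = 2(1.96 + 0.84)²/d², which gives 175 for d = 0.3 and 393 for d = 0.2.
- Design effect 1 + 30 × 0.037 = 2.11.
- Total for 0.3: 2 × 175 × 2.11 = 738.5 (plan: 738).
- Total for 0.2: 2 × 393 × 2.11 = 1658.5 (plan: 1658).

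The usual form 1 + 29 × 0.037 = 2.073 gives 725.6 and 1629.4, within 3%. Either way, the plan's figures are built on the class as the cluster, in agreement with the pilot, Stage 1 and Stage 2 text.

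**2. Does the pre-test covariate absorb the ICC?** Suppose the pre/post correlation r is the same at pupil and class level. Adjustment then multiplies both variance components by (1 − r²). With r = 0.6 (assumed), the remaining ICC is 0.64 × 0.037 / 0.64 = 0.037. Adjustment improves precision, but the share of variance lying between classes is unchanged.

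**3. Expected type I error if class is ignored.** The true standard error exceeds the reported one by about √(1 + 29 × ICC), so a nominal 1.96 is really 1.96/√(1 + 29 × ICC).

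- Class ICC 0.037: √2.073 = 1.440; 1.96/1.440 = 1.361; two-sided tail about 17%.
- Class ICC 0.0185: √1.5365 = 1.240; 1.96/1.240 = 1.581; two-sided tail about 11%.

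**4. Simulation.** The layout follows the Participants section: 7 schools of about 150 pupils, taken as 5 classes of 30, so 35 classes and 1050 pupils. Five classes cannot split evenly, so each school is allocated 3:2 or 2:3. The pre/post correlation is 0.6, with 1500 runs per scenario. The plan gives one ICC, so its split between school and class is assumed.

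Two-sided type I error at nominal 5%:

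| ICC school / class | Pupil-level, pre-test only | Pupil-level + school | Class-level, no school | Class-level + school |
|---|---|---|---|---|
| 0 / 0.037 | 17.9% | 18.2% | 5.3% | 5.1% |
| 0.0185 / 0.0185 | 11.5% | 10.8% | 3.1% | 4.5% |
| 0.037 / 0 | 6.0% | 4.6% | 1.3% | 4.1% |
| 0.037 / 0.037 | 20.3% | 17.9% | 2.9% | 5.5% |

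The pupil-level results for the first two rows agree with step 3. Adding school to the pupil-level model brings the error to about 5% only where there is no class-level ICC. The treatment estimate is unbiased in every cell.

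Power at a true effect of 0.2, class-level analysis:

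| ICC school / class | Without school | With school |
|---|---|---|
| 0 / 0.037 | 0.77 | 0.74 |
| 0.0185 / 0.0185 | 0.81 | 0.87 |
| 0.037 / 0.037 | 0.62 | 0.73 |

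The last row has a total ICC of 0.074, twice the plan's value.

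**The case against.** **The form of the model is left open, and this is a condensed article.** A list of stratification covariates commonly sits in the analysis plan, and the wording does not forbid a class or school term. That would answer a complaint about silence. It does not answer this one, because the section states how clustering will be handled and the stated method is inadequate. The objection does stand for school taken alone: its absence from an article would not be worth raising by itself.

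**The covariate may help more than assumed.** If class means are more stable over time than individual scores, pre-test adjustment would lower the remaining class-level ICC and the inflation would be smaller. That is possible. Nothing in the plan shows it, and variation introduced on the intervention day cannot be predicted by a score taken weeks before.

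**Leaving out school is harmless or safe.** Once class is in the analysis, this is largely right: the estimate is unbiased and the test errs on the conservative side. What remains is a loss of power when schools differ, and its size depends on the assumed split.

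**Stronger readings that the plan does not support.** A reader might infer from the school-level phrase in Method/Design that whole schools are randomised, and conclude that the power statement collapses. The same sentence goes on to assign classes, Stage 1 speaks of class randomisation, the fidelity check needs both conditions in each school, and the sample size uses classes of 30. The phrase is loose wording for allocation carried out school by school, so a design effect for whole schools has no place here. A reader might also infer that the omitted school term makes standard errors too large. That holds only for an analysis that already respects class. With class-level correlation present, the pupil-level model errs in the opposite direction.

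**Conclusion.** The concern holds in this form: the stated analysis does not follow the design, chiefly because it has no term for class and relies on the pre-test score instead. At the plan's own ICC of 0.037, type I error for a pupil-level model is about 18% if all of the clustering lies at class level and about 11% if half does. It reaches about 20% if a further 0.037 lies at school level. If all of it lay at school level the error would be near nominal (6.0%), but that is hard to square with a sample size that treats the class as the cluster.

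The missing school term is secondary. With class respected and schools differing, leaving it out lowers power at an effect of 0.2 from 0.87 to 0.81 (split 0.0185/0.0185) or from 0.73 to 0.62 (split 0.037/0.037).

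These figures rest on the assumed ICC splits, a pre/post correlation of 0.6 at every level, and equal classes of 30. The direction of the class effect does not depend on the exact values. The allocation wording is a minor point of clarity.

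**What to change.** **Analysis section.** Specify the primary model as a linear mixed model with condition, a random effect for class, school as a fixed effect, and pre-test score as a covariate, with a small-sample correction to the degrees of freedom. A class-level analysis of means with the same school and pre-test terms is an acceptable alternative with about 35 classes. Describe the pre-test covariate as serving precision, and remove the statement that it deals with clustering.

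**Method/Design and Stage 1.** Reword both allocation sentences to say that classes are randomised to condition within each school, with school as the block.

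**Cost.** There is no change to recruitment, allocation or data collection. The school term uses 6 degrees of freedom. If schools do not differ at all, that costs about 2% in standard error (power 0.74 instead of 0.77 in the first row of the power table). The random class effect gives wider intervals than the pupil-level model, but these reflect the clustering that the sample size already allows for.
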